For reducing the influenza disease burden, influenza vaccination has demonstrated significant efficacy and cost-effectiveness, particularly within populations at high risk of infection [21, 22]. The immune responses induced by influenza vaccines are typically specific to the particular viral strain. The presence of antibodies specific to a certain type or subtype of influenza virus typically offers minimal or no immunity against other types or subtypes. Furthermore, such antibodies usually do not protect against antigenic variants of the same virus that emerge due to antigenic drift. Vaccination can potentially induce a “back boost” of antibody titers specifically targeting influenza A(H3N2) viruses in the adult population. Influenza vaccines are administered on an annual basis due to the occurrence of antigenic drift and shift. The efficacy of these vaccines, which typically ranges between 40% and 60%, exhibits considerable variation across different settings and influenza seasons [10]. In addition, the findings of a systematic review indicated that out of the 118 studies examined, 22 studies demonstrated that influenza vaccination resulted in cost savings [23]. This study’s findings also stated that there were 13 studies reporting cost-effectiveness ratios of $10,000 per outcome, another 13 reporting ratios ranging from $10,000 to $50,000 per outcome, and three reporting ratios equal to or exceeding $50,000 per outcome [23]. Although the cost-effectiveness of influenza vaccination has been established, it is necessary to note that the applicability of cost-effectiveness parameters may vary across different countries due to variations in influenza disease profiles, unit costs of vaccination, and health system delivery mechanisms [24]. Hence, it is imperative to have country-specific estimates to allocate limited resources effectively.

Bangladesh lacks context-specific data on the acceptability, cost-effectiveness, and vaccination capacity needed for influenza vaccination among the WHO-defined high-risk population, which hinders informed vaccination strategies.

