## Study size

### Sample size and sampling

#### The sample size for the vaccine acceptability objective

Our study design will be quasi-experimental. Our primary outcome for vaccine acceptability is the intention to receive the influenza vaccine. Based on studies utilizing the high-risk group-specific health belief model conducted in neighboring countries, it has been found that 91% of elderly people, 88% of adults with chronic illness, 76.3% of pregnant women, and 62.4% of parents with six to three-year-olds expressed their intention to get the influenza vaccine [38–40, 45]. We expect a similar positive intention to receive the influenza vaccine, ranging from 62 to 91% for our target study population. In this study, we employed a significance level of 5%, a power of 80%, a design effect of 1.2, and account for a non-response rate of 10% to determine the required sample size [65–67]. We will utilize a validated health belief model tool. To avoid selection bias, we will use random assignment to the study based on predefined inclusion and exclusion criteria. We will also provide training to study staff about random enrolment of the study participants based on inclusion and exclusion criteria. Table 5 represents the estimated sample size by the high-risk group for the vaccine acceptability objective.

**Table 5 Tab5:** Estimated sample size for investigating the vaccine acceptability/ intention to receive, health outcome due to vaccination, and cost-effectiveness of implementing a facility-based influenza vaccination

High-risk group	The sample size for the vaccine acceptability survey	The sample size for vaccine effectiveness	The sample size for the cost-components survey
Children 6 months to 8 years	659	465	60
Pregnant women	495	756	39
Elderly ≥ 60 years	330	736	56
Adults with chronic diseases	425	610	31

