#### The sample size for the vaccine effectiveness objective

Our primary outcome for health outcome for vaccination is vaccine efficacy against influenza among high-risk group populations. Studies from neighboring countries found that ILI symptoms were 15.30% of children, 31.23% of adults with chronic illness, 10.97% of pregnant women, and 20% of the elderly [68–70]. A systematic review of seasonal influenza vaccine policy, use, and effectiveness also revealed that pooled vaccine effectiveness for high-risk groups in the tropics and subtropics ranged from 48 to 88% (10). We expect a similar vaccine efficacy between 50 and 81% for our study’s targeted high-risk group population. A 5% significance level, 80% power, design effect 1.2, and 10% non-response were used to calculate the required sample size to estimate vaccine effectiveness [65–67]. Table 5 represents the high-risk group’s estimated sample size for vaccine effectiveness.

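### No single reading of Table 5 yields all four vaccine-effectiveness sizes from the stated inputs; the elderly (736) and chronic-disease (610) sizes exceed what an efficacy of 50-81% can require at 1:1.

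*Protocol article*

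**What the plan says.** The section on the sample size for the vaccine effectiveness objective gives the ILI risks: "ILI symptoms were 15.30% of children, 31.23% of adults with chronic illness, 10.97% of pregnant women", and "20% of the elderly". It cites a review in which pooled effectiveness "ranged from 48 to 88" per cent, and then sets the planning range: "We expect a similar vaccine efficacy between 50 and 81" per cent. The remaining inputs are common to all groups: "A 5% significance level, 80% power, design effect 1.2, and 10% non-response were used".

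The resulting sizes are in Table 5, in the column headed "The sample size for vaccine effectiveness": children 465, pregnant women 756, elderly 736, adults with chronic diseases 610. The article does not say whether these are totals or per hospital, what the allocation ratio is, whether the test is one- or two-sided, or which efficacy belongs to which group. The section on vaccine efficacy estimation calculates effectiveness with a confidence interval separately for each risk group, so each row of the table has to stand on its own.

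**The concern.** The article prints both the inputs and the outputs of a calculation, and two of the four outputs lie outside what the inputs can give under the usual two-group comparison. An article may leave formulas and per-group assumptions to the full protocol, and that omission alone would not be a finding. The finding is that the printed figures disagree with one another.

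What is at stake is the claim of 80% power in every group. Depending on what the sizes mean, two groups may have much less than 80% at the bottom of the plan's own efficacy range, while the other two have much more. The group-specific estimates are of policy interest in their own right, and the cost-effectiveness analysis is also done by risk group.

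**Working it through.** **Inputs.** From the vaccine-effectiveness sample size section: control risk p1 = 0.153 (children), 0.1097 (pregnant women), 0.20 (elderly), 0.3123 (chronic disease); efficacy VE = 0.50 to 0.81; alpha 0.05; power 0.80; design effect 1.2; non-response 10%. Assumed because not stated: two-sided test, 1:1 allocation.

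**Formula.** With p2 = p1(1 − VE), d = p1 − p2 and p̄ = (p1 + p2)/2,

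n per arm = [1.96·√(2p̄(1 − p̄)) + 0.8416·√(p1(1 − p1) + p2(1 − p2))]² / d²,

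rounded up, then multiplied by 1.2/0.9, and by 2 for a total.

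**Reproducing the plan's figures.** Read as totals, two rows come out:
- Children at VE 60%: n = 177; 177 × 1.2/0.9 = 236; total 472. The listed 465 corresponds to VE of about 60.4%.
- Pregnant women: the listed 756 corresponds to VE of about 57.5%.

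The other two do not. The requirement is largest at the lower bound, VE 50%:
- Elderly: p2 = 0.10, p̄ = 0.15, d = 0.10. n = (0.990 + 0.421)²/0.01 = 199.0, taken as 199. Total = 2 × 199 × 1.2/0.9 = 531. Listed: 736, a ratio of 1.39.
- Chronic disease: p2 = 0.1562, p̄ = 0.2342, d = 0.1562. n = (1.174 + 0.495)²/0.0244 = 114.3, rounded up to 115. Total = 2 × 115 × 1.2/0.9 = 307. Listed: 610, a ratio of 1.99.

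| Group | Listed | Total needed, VE 50% / 81% | VE implied if total | VE implied if per arm |
|---|---|---|---|---|
| Children | 465 | 725 / 224 | 60% | 45% |
| Pregnant women | 756 | 1,048 / 323 | 57.5% | 43% |
| Elderly | 736 | 531 / 165 | 43% | 31% |
| Chronic disease | 610 | 307 / 96 | 36.5% | 26% |

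The per-arm requirement at VE 50% is half the total (about 363, 524, 266 and 154), and every listed size is above it. So on the per-arm reading no row fits.

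**Robustness.** With a continuity correction the ceilings rise only to about 583 (elderly) and 338 (chronic disease). A one-sided test moves the implied VE further down (totals: 39% and 33%). With unequal allocation, three controls per vaccinated participant at VE 50% needs 741 in the elderly (733 if non-response is handled as × 1.1), close to 736. For chronic disease, even a 4:1 split in favour of controls with continuity correction needs only 549. Lowering VE to 48%, the bottom of the cited review range, raises that to 597, still below 610.

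**Power of the listed sizes.** Effective n per arm = (N/2) × 0.9/1.2 = 174, 284, 276 and 229 if N is a total, and twice that if per arm.

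| Group | VE 50%, total | VE 50%, per arm |
|---|---|---|
| Children | 61% | 89% |
| Pregnant women | 66% | 92% |
| Elderly | 91% | over 99% |
| Chronic disease | 98% | over 99% |

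Read as totals, power at VE 60% is 79% for children and 84% for pregnant women; at VE 65% it is 87% and 90%. At VE 81% every group has at least 98%.

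**The case against.** The strongest reply is that the article gives a range of efficacy and not one value, so each group may have had its own. That explains 465 and 756 if they are totals. It also disposes of a tempting shortcut, that chronic disease, with the highest ILI risk, must need the fewest participants: this holds only at equal efficacy. It does not rescue 736 or 610, because the comparison above already uses the efficacy in the range that needs the most participants.

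A second reply is that the sizes may rest on something other than a 1:1 two-proportion test. An unstated split of about 3:1 would nearly explain the elderly figure. Sizing for precision can also be made to fit. With an assumed half-width of 17.5 percentage points for the effectiveness estimate, a total reading and × 1.1 for non-response, the implied efficacies are 81.0%, 78.5%, 63.5% and 51.4% for children, pregnant women, elderly and chronic disease. But that half-width is nowhere in the article, and the method makes no use of the 80% power the article says was used. It shows only that one cannot claim the sizes fit no conceivable method.

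A third reply is that the low powers are a worst case. That stands: 61% and 66% need both the total reading and an efficacy at the 50% bound.

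A reader might also bring in the Background, where efficacy "The efficacy of these vaccines, which typically ranges between 40% and 60" per cent, and argue for power at 40%. That range is a general one across settings and seasons, while the sample size section relies on a pooled range for high-risk groups in the tropics and subtropics. The two are not in strict conflict, and the point does not need the comparison.

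**Conclusion.** The elderly and chronic-disease sizes do not follow from the printed inputs under a two-sided two-proportion comparison with 1:1 allocation, and no single reading of Table 5 gives all four sizes at the stated 80% power. Read as totals, these two sizes are about 1.4 and 2.0 times the most the efficacy range can require. Read per arm, all four are too large for it.

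Two stronger inferences are not supported. A reader might conclude that none of the sizes can be derived, but the children and pregnant-women sizes can, as totals. A reader might also conclude that the study is short of power throughout. The elderly and chronic-disease groups are oversized for the stated inputs, with at least 91% and 98% power anywhere in the range, and a shortfall for children and pregnant women arises only if the sizes are totals and efficacy is near 50%.

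The result assumes two-sided testing and takes the ILI risks as given, as the risk in unvaccinated participants. An unstated unequal split could account for the elderly figure, but not for chronic disease within the splits checked (1:4 to 4:1).

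**What to change.** Correct 736 and 610, or state the assumption that produces them. Label the vaccine-effectiveness column of Table 5 as total or per hospital, and give the efficacy and allocation used for each group. Replace the uniform 80% with the power each listed size has at that efficacy and at the 50% lower bound. The powers tabulated above should not be copied in until the total or per-hospital basis is settled, since they differ by up to 28 percentage points between the two (children: 61% against 89%).

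Moving surplus places from the elderly and chronic-disease groups to children and pregnant women is worth considering only if the sizes prove to be totals and enrolment still allows it; the abstract gives March 2022 for the first participant. Otherwise the change is to one table and one or two sentences, with no additional participants.

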#### The sample size for the cost-components survey

Our primary outcome for costs-components is the total influenza-associated illness costs among high-risk group populations. A study conducted in Bangladesh examined the economic assessment of diseases associated with influenza [3]. The findings indicated that the overall direct costs related to influenza-induced illness were estimated at USD 70 (7,614 Taka) for children under the age of five [3]. Pregnant women incurred costs of USD 191 (20,808 Taka), while the elderly faced expenses of USD 126 (13,761 Taka) [3]. Adults with chronic diseases had direct costs amounting to USD 75 (8,222 Taka) [3]. Our study anticipates a comparable aggregate direct cost of influenza-related illness ranging from USD 70 (7,614 Taka) to USD 191 (20,808 Taka) for the specific population of high-risk individuals we targeted. Other than that, our study employed a significance level of 5%, a power of 80%, a design effect of 1.2, and accounts for a non-response rate of 10% to determine the appropriate sample size [65–67]. Table 5 represents the high-risk group’s estimated sample size for vaccine effectiveness. For both of our objectives, we will screen and enroll study participants from both inpatient and outpatient across all clinical departments of the study hospitals, who will be seeking routine care and treatment at the study hospitals.

#### Quantitative variables

We will conduct a thorough literature review to help us choose the quantitative variables for our study, drawing upon a range of sources [5, 31, 36–44]. The variables will be categorized into three broad categories. Firstly, we will encompass sociodemographic variables, which consist of a wide range of sociodemographic data related to the specific high-risk group being studied. Secondly, in the medical history section, we included variables regarding the medical history of individuals at high risk and any common signs and symptoms they experienced in the previous 30 days. The third category includes direct and indirect cost components related to using medical resources for SARI and ILI. These variables include expenses that occur before, during, and after receiving treatment for SARI and ILI. This provides a thorough understanding of the economic factors associated with these conditions.

## Statistical methods

We will summarize all the data using various descriptive statistics tools, such as frequency, percentage, mean, median, standard deviation (SD), and interquartile range (IQR, calculated as the difference between the 25th percentile and the 75th percentile).

### Objective specific data analysis plan is as follows

#### Data analysis on the propensity to vaccine using results from the vaccine acceptability survey

In each of the five HBM constructs, we will use factor analysis using the principal axis factor technique and varimax rotation to find latent variables and minimize the number of independent variables. The Kaiser-Meyer-Olkin test will be used to determine sample adequacy. The parameters that suggest an acceptable fit on the factor analysis will be the goodness of fit index (GFI) and root mean square error of approximation (RMSEA) [71]. We will also use Cronbach’s alpha to assess the internal consistency of survey items [45]. We will use the regression models with robust error estimation to predict and understand the association between influenza vaccination status and all five HBM constructs.

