### Study setting

We selected study hospitals considering several factors. Firstly, we will use the hospital-based influenza surveillance (HBIS) platform to conduct this study. We have chosen Rajshahi Medical College Hospital and Khulna Medical College Hospital for our study activities on high-risk groups’ vaccine acceptability and cost-effectiveness. We will enroll Severe acute respiratory illness (SARI) and influenza like illness (ILI) patients identified from the HBIS platform to meet our study objectives. We will also collect influenza virus test results from the HBIS platform and data on influenza illness episodes’ costs from the influenza-positive SARI and ILI patients. This approach will save influenza virus testing costs not allocated in the current study budget. Secondly, to assess the outcome of influenza vaccination, we plan to enroll patients from public tertiary-level hospitals (one treatment/vaccinated and the other control hospital) to minimize baseline differences between the treatment/vaccinated and control arm. Thirdly, we have chosen Ragib-Rabeya Medical College & Hospital to represent public and private healthcare facility cost differences while estimating the costs of influenza illness. A brief description of the study sites’ bed occupancy rate and average monthly admission are represented in Table 2 [29, 30].

**Table 2 Tab2:** Demographic characteristics of the study hospitals

Study sites	Bed occupancy rate (%)	Total no OPD visits	Total number of PNC visits	Total number of admission	Middle wealth quantile
Rajshahi Medical College Hospital	198.05	114,818	2,405	22,022	24.1%
Khulna Medical College Hospital	275.00	35,311	991	8,859	24.8%
Jalalabad Ragib-Rabeya Medical College & Hospital	NA	NA	NA	NA	15.8%

Source: Local health bulletin October 2022

OPD = outpatients care department; PNC = post-natal visit

Note: a bed occupancy rate greater than 100% indicates that these hospitals receive and care for more patients than their capacity

Study sites for influenza vaccine acceptability, health beliefs, barriers:

We will conduct a health belief model (HBM) survey in two conveniently selected hospitals:

Rajshahi Medical College Hospital, Rajshahi.Khulna Medical College Hospital, Khulna.

Study sites for influenza vaccination cost-effectiveness objective:

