### Variables

We thoroughly reviewed the literature on different outcome variables and explanatory factors in our research [5, 31, 36–44]. Regarding our first objective, which centered on vaccine acceptability, our primary outcome of interest wil be the high-risk groups’ intention to receive the influenza vaccination. This will assist us in assessing the propensity of high-risk groups’ willingness to receive influenza vaccine. Our second objective focuses on vaccination effectiveness, precisely measuring vaccine efficacy against influenza in high-risk group groups. This metric will enable us to assess the efficacy of the vaccination in protecting high-risk group groups. In addition, we will thoroughly examine the cost components related to influenza, focusing on the overall costs of influenza-related illnesses in high-risk groups as our second objective’s variables. To understand the complex factors that affect vaccine acceptance and effectiveness, we will examine various explanatory variables, including age, gender, occupation, location, marital status, and income, among others.

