### Data sources and measurement

#### Data collection to assess health beliefs, barriers, and intention to receive an influenza vaccine

We will collect data on acceptability, health beliefs, obstacles, and current intentions to receive the vaccine from enrolled participants (Fig. 2). We will capture these data using the health belief model (HBM). The questionnaire has been developed using an existing literature review [36–41, 45]. We will include items to assess five theoretical constructs of HBM based on reviewing relevant literature, including high-risk individual’s perceived susceptibility to disease, perceived severity of influenza, perceived benefits of the vaccine, perceived barriers to the vaccine, cues to action, and self-efficacy [37, 38, 46]. We will conduct face-to-face interviews for the data collection.

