### Data collection to determine vaccination cost-effectiveness

#### Vaccination campaign

To record health outcomes after influenza vaccination, in one of the two public tertiary-level study hospitals, we will conduct an influenza vaccination campaign before the influenza season, where the vaccine will be offered free of cost to high-risk patients, and in the second hospital, vaccination will not be offered. We will work with the hospital administration to set up a vaccination booth on the hospital premises. Vaccines will be made available at the vaccination booths. Posters and leaflets containing information on influenza vaccination will be displayed at the vaccination booths and key hospital locations with information on the vaccination. Inpatients and outpatients of all departments will be informed about the ongoing immunization campaign. Eligible patients will be offered to take the vaccine during the vaccination campaign. Benefits, significance, adverse effects, and how to manage them will be explained to the patients. Nurses/ Health Assistants (HA) will provide influenza vaccination throughout the campaigns. At 8 AM, the vaccination booth will open and close at 2 PM, six days a week throughout the campaign period. A vaccination card will be issued to the participants. All high-risk groups will get one dose of seasonal influenza vaccination (Quadrivalent), except children aged six months to 8 years, who will receive two doses four weeks apart [31, 32]. All vaccines will be the southern hemisphere vaccine as recommended by the WHO for Bangladesh. Regarding children, we will make phone follow-ups with the guardians of the children receiving the first dose to remind them about the second dose schedule, and it will be recorded in the vaccine card if the second dose is received. In order to ensure the availability and quality control of vaccines throughout the three-month campaign period, the research team at icddr,b will closely monitor the campaign. All vaccinated participants will receive notification regarding potential adverse events following immunization (AEFI) during the vaccination process. To document any untoward occurrences after Adverse Events Following Immunization (AEFI), we will adhere to the pre-existing surveillance mechanism implemented by the World Health Organization (WHO) and the Ministry of Health and Family Welfare (MoHFW) of the government of Bangladesh. During the vaccination campaign briefing session in each study hospital, participants will be informed about the process of reporting any Adverse Events Following Immunization (AEFI) within the hospital’s established surveillance system. Additionally, participants will be provided with the mobile number, as stated in the consent form, to report any such issues. Furthermore, during the vaccination campaign implementation, a representative from icddr,b will be assigned to each study hospital to oversee and monitor any adverse events following immunization (AEFI) in conjunction with the hospital’s existing surveillance system. If an Adverse Event Following Immunization (AEFI) case is identified, the personnel affiliated with icddr,b will promptly notify the Hospital Surveillance Officer (HSO), provide support to the HSO in completing the AEFI report form, and subsequently transmit it to the Expanded Programme on Immunization (EPI) headquarters via the Chief Health Officer.

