
In the second hospital, we will enroll participants meeting the high-risk group individual criteria. However, no vaccination campaign will be conducted. We will name this group as an unvaccinated cohort.

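### The only regression stated for the acceptability survey models vaccination status, not the declared primary outcome of intention, and one of the two survey hospitals does not offer the vaccine

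*Protocol article*

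**What the plan says.** On the outcome, the Variables section states for the first objective that "our primary outcome of interest wil be the high-risk groups’ intention to receive the influenza vaccination". The section on the sample size for the acceptability objective repeats it: "Our primary outcome for vaccine acceptability is the intention to receive the influenza vaccine". That section plans on intention proportions from neighbouring countries: 62.4% (parents of young children), 76.3% (pregnant women), 88% (adults with chronic illness) and 91% (elderly). The data-collection section says that the survey records "current intentions to receive the vaccine from enrolled participants".

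On the analysis, the section on the propensity to vaccinate describes factor analysis, reliability checks and then one family of regressions with robust errors, for the "association between influenza vaccination status and all five HBM constructs". No regression of intention is described.

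On the sites, Study setting says: "We will conduct a health belief model (HBM) survey in two conveniently selected hospitals". It names Rajshahi and Khulna, the same pair listed for health outcomes. The Vaccination campaign section says that one hospital runs the campaign, and "in the second hospital, vaccination will not be offered". Of the participants enrolled there it says: "We will name this group as an unvaccinated cohort".

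On the constructs, the data-collection section says "We will include items to assess five theoretical constructs of HBM" and then lists six: susceptibility, severity, benefits, barriers, cues to action and self-efficacy. The analysis section again counts five.

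**The concern.** The outcome that is declared, measured and used for sizing is not the one that the stated model uses. Taken literally, the plan regresses a variable that the design itself controls. At the hospital without a campaign, a respondent who strongly wants the vaccine and one who would refuse it have the same study vaccination status. A model of that status mixes the effect of beliefs with the effect of which hospital the person attended.

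The article says in its Discussion that the acceptance survey will inform interventions to raise uptake. Estimates of which beliefs drive acceptance are therefore a main product of this objective, and the dependent variable decides what they mean.

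**Working it through.** **1. The plan's own figures.** Table 5 gives 659 (children), 495 (pregnant women), 330 (elderly) and 425 (chronic disease), so 659 + 495 + 330 + 425 = 1,909. The stated inputs are 5% significance, 80% power, design effect 1.2 and 10% non-response, with no precision or detectable difference. The four sizes therefore cannot be derived from the text. For example, a one-sample test of a 6-point increase, n = [1.96·√(p₀(1−p₀)) + 0.842·√(p₁(1−p₁))]² / 0.06², inflated by 1.2 and by 1/0.9 or 1.1, gives 660–666 for children and 489–494 for pregnant women, but only 182–184 for the elderly and 257–260 for chronic disease. The present point does not depend on this. What matters is that every planning proportion is an intention proportion and none is a vaccination rate.

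**2. Respondents whose study status is set by site.** The split of the survey between hospitals is not stated. With share s at the hospital without vaccine, the number is 1,909 × s:

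| s (assumed) | Respondents |
|---|---|
| 30% | 573 |
| 50% | 955 |
| 70% | 1,336 |

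The proportion vaccinated through the study cannot exceed 1 − s. At s = 50% this ceiling is 50%, below all four planning proportions (62.4% to 91%). Status therefore cannot stand in for the quantity that the survey was sized on.

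**3. Effect on the belief estimates.** Assumed for illustration only: equal hospital sizes, and uptake at the offering hospital of 80% with high belief and 40% with low belief. The true risk ratio is 0.80/0.40 = 2.0 and the true odds ratio is (0.80/0.20)/(0.40/0.60) = 6.0. Uptake at the other hospital is taken as 0. Let a and b be the high-belief shares at the offering and non-offering hospital. Pooled without site:

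- uptake with high belief = 0.80·a/(a + b)
- uptake with low belief = 0.40·(1 − a)/[(1 − a) + (1 − b)]

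| a, b | High belief | Low belief | Pooled risk ratio |
|---|---|---|---|
| 50%, 50% | 40% | 20% | 2.0 |
| 60%, 40% | 48% | 16% | 3.0 |
| 40%, 60% | 32% | 24% | 1.33 |

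With balanced beliefs (first row) the risk ratio is unchanged. The risk difference halves from 40 to 20 points, and the odds ratio falls from 6.0 to (0.40/0.60)/(0.20/0.80) = 2.67. On the log scale that is 0.981/1.792 = 0.547 of the true value. With unbalanced beliefs the risk ratio is biased as well, in either direction.

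**4. With hospital in the model.** Confounding by site is removed, but a hospital with no vaccinated respondents contributes nothing to the belief coefficients. The loss is then of information: about half of the survey under an equal split.

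**The case against.** The strongest reply is that vaccination status is loose wording for intention. The heading of the analysis section speaks of propensity and of the acceptability survey, and Variables uses propensity for willingness. On that reading the site problem disappears. This is plausible, but the section never says it, and an analyst who follows the text would model status. The phrase might instead mean past vaccination, which is not the declared outcome either.

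Second, the article gives no covariate list for this model, which may properly sit in a fuller document, and Variables includes location among the explanatory factors. This stands: pooling without site is an assumption, and with site included the harm is lost information rather than bias.

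Third, the article pairs two public tertiary hospitals in order to limit baseline differences. That is a reasonable aim, but the hospitals were chosen for convenience, and nothing shows that health beliefs are balanced between them.

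A reader might also infer more than the text supports:

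- That Khulna is the hospital without vaccine. The article speaks only of one hospital and the second hospital.
- That nobody there is vaccinated. Vaccine obtained elsewhere is not ruled out, and the Background notes free vaccine for Hajj pilgrims.
- That belief effects are necessarily attenuated. With balanced beliefs this holds for the odds ratio and the risk difference, not for the risk ratio, and the article names no effect scale.
- That intention goes unanalysed. The general descriptive statistics cover it; what is missing is a model of its determinants.
- That a measured construct will be dropped. Five against six may be a simple miscount.

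**Conclusion.** The point holds. The article fixes a dependent variable for the acceptability regression that differs from the primary outcome it declares twice and sizes on. This is a contradiction within the document, not a detail left to an analysis plan. Because one survey hospital does not offer vaccine, the difference is substantive: about 955 of 1,909 respondents under an assumed equal split (573 to 1,336 for 30% to 70%) would have a study vaccination status that says little or nothing about their beliefs. The risk ratios of 3.0 and 1.33 against a true 2.0 show the possible direction and scale of confounding if site is left out. They rest on assumed uptake, assumed belief shares, equal hospital sizes and no outside vaccination, and they are not predictions. The mismatch in the number of constructs is a real inconsistency, but a lesser one.

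**What to change.** In the analysis section for the acceptability survey, replace influenza vaccination status with intention to receive the influenza vaccine as the dependent variable, state that both hospitals are used, and include hospital as a covariate. How intention is coded, and whether the four risk groups are modelled separately or together, can be left to the authors.

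If actual uptake is also to be modelled, restrict that model to the hospital that offers the vaccine and label it secondary.

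Reconcile the count of five constructs with the six listed, in both the data-collection and the analysis sections.

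The cost is wording only. Table 5 is already planned on intention and does not change, and since the survey already records intention, no new data are needed.
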